## **9.0 STATISTICS**

### **9.1 Statistical design**

This is a non-randomised open label study of influenza vaccine response to an enhanced immunisation schedule in a population of paediatric patients treated for cancer.

The primary aim will be to assess the within-patient differences in immune response after repeat doses of the inactivated influenza vaccine in children and adolescents who are being treated for cancer: for those  $\geq 9$  years of age comparing two doses to one dose, and for those  $< 9$  years of age comparing three doses to two doses.

Two separate methods of immune response evaluation will be assessed:

1. The humoral response will be assessed by measuring HI antibodies in participants' sera produced by stimulated B-lymphocytes in response to the influenza vaccine.
2. The cellular response will be assessed by measuring INF- $\gamma$  produced by stimulated T-lymphocytes *in vitro* in response to an influenza vaccine concentrate.

One of the secondary aims will be to assess variables predictive of influenza vaccine immune response. The variables will include participant age, sex, type of disease/treatment and parameters of baseline immune function including total lymphocyte count, B-cell and T-cell count, NK cell count, memory cell count and immunoglobulin levels.

### **9.2 Sample size estimation**

Sample size calculations have been based on differences in the paired proportions of vaccinated children demonstrating immunogenicity (seroprotection and seroconversion) after the standard number of doses and the extra dose, respectively. If the immunogenicity status of 15% of participants changes over the two time-points, 60 participants would have 80% power to detect an increase of 13.7% in the seroprotection and seroconversion rates and 80 participants would have 80% power to detect an increase of 12.0% (McNemar test,  $\alpha=0.05$ ). If discordancy in the immunogenicity status is observed in 20% of participants, the study would have 90% power to detect differences in rates of 18.1% and 15.8% for 60 and 80 participants, respectively. These rate increases would seem reasonable given increases achieved in healthy children after fewer doses.

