### **2.2 Efficacy objectives**

#### **2.2.1 Primary efficacy objectives**

- To determine whether an enhanced influenza vaccine schedule improves the immune response to inactivated influenza vaccine in children undergoing treatment for cancer.
  - a. In children  $\geq 9$  years of age - to determine whether two doses of influenza vaccine (given at least four weeks apart) are superior to one dose.
  - b. In children  $< 9$  years of age - to determine whether three doses of influenza vaccine (each given at least four weeks apart) are superior to two doses.
- To determine whether measurement of cellular immune response to the inactivated influenza vaccine provides a better surrogate end point for vaccine efficacy than influenza-specific hemagglutinin inhibition (HI) antibody titers in immunocompromised children with cancer.

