### **3.7 Number of participants**

It is estimated that 80 subjects will be recruited over the study period. This is based on the incidence and prevalence of patients receiving diagnosis and treatment for cancer at Perth Children's Hospital Haematology and Oncology Department.

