### **9.3 Statistical analysis**

The primary immunogenicity endpoints will be the percentage of participants achieving seroprotection and seroconversion. To assess if the extra vaccination dose improves immunogenicity, a McNemar test will be used to assess the

difference in these percentages as calculated from the immunogenicity status obtained after the last two doses of each individual. We will also evaluate geometric mean titers of HI antibodies at baseline and after vaccination. The geometric mean fold increase (GMFI), with 95% confidence intervals, will be calculated for each strain, using a log-normal approximation for the distribution of HI antibody levels pre and post vaccination.

Multivariate logistic regression models will be used to assess the influence of clinically relevant demographic and immunological variables to predict seroconversion to each influenza vaccine strain and complete seroconversion to all strains of the vaccine. Linear regression analyses of log-transformed HI antibody titers and log-transformed T-lymphocyte IFN- $\gamma$  levels will be undertaken to assess the influence of clinically relevant variables on humoral and cellular responses to vaccination, respectively.

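### The power quoted in Section 9.2 is for one test on all 60 or 80 children; the two age-specific primary questions cannot both have it

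*Protocol*

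**What the plan says.** Section 2.0 (Specific hypothesis) sets out two hypotheses, one for children of 9 years and over (two doses against one) and one for children under 9 (three against two). Section 2.2.1 makes them primary objectives (a) and (b) beneath a general objective about an enhanced schedule. Objective (b), for example, is "to determine whether three doses of influenza vaccine (each given at least four weeks apart) are superior to two doses". Section 9.1 describes the primary aim in the same age-specific terms.

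On numbers, Section 3.7 says "It is estimated that 80 subjects will be recruited over the study period". No split by age is given.

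Section 9.2 gives four power statements, all on total numbers:

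- "If the immunogenicity status of 15% of participants changes over the two time-points", then "60 participants would have 80% power to detect an increase of 13.7" percentage points and "80 participants would have 80% power to detect an increase of 12.0" percentage points.
- "If discordancy in the immunogenicity status is observed in 20% of participants", then "90% power to detect differences in rates of 18.1% and 15.8% for 60 and 80 participants, respectively".

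Section 9.3 names a McNemar test on the "difference in these percentages as calculated from the immunogenicity status obtained after the last two doses of each individual". It does not say whether the test covers all children together or each age group.

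**The concern.** The two contrasts differ in number of doses, in the pair of visits compared and in the children who supply the data. A reader who sees 80% or 90% power in Section 9.2 will attach it to the hypotheses in Section 2.0. Those hypotheses each rest on only a share of the 80 children.

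Two errors could follow. A non-significant result in one age group could be read as an adequately powered negative when it was not. A significant result over all children could be taken as support for both new schedules when the gain lay in one age group. The protocol aims at guideline recommendations, and the schedules it studies differ by age.

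**Working it through.** **Inputs from Section 9.2.** McNemar test, α = 0.05 (taken as two-sided, which reproduces the figures); discordant share ψ = 15% or 20%; N = 60 or 80; differences d = 13.7, 12.0, 18.1 and 15.8 points.

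**Formula.** The plan does not name one. The usual normal approximation for paired proportions is

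power = Φ[(d√n − 1.96√ψ) / √(ψ − d²)].

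**Step 1: the plan's own figures.** For N = 80, ψ = 0.15, d = 0.12: (0.12 × 8.944 − 1.96 × 0.3873) / √(0.15 − 0.0144) = 0.314 / 0.368 = 0.853, and Φ(0.853) = 80.3%.

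| N | ψ | d (points) | Stated power | Recomputed |
|---|---|---|---|---|
| 60 | 15% | 13.7 | 80% | 79.8% |
| 80 | 15% | 12.0 | 80% | 80.3% |
| 60 | 20% | 18.1 | 90% | 90.1% |
| 80 | 20% | 15.8 | 90% | 90.0% |

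All four agree, and each uses every child in a single test.

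**Step 2: numbers needed per question.** Solving the formula for n gives 79.4 children for +12.0 points at 80% power and 79.9 for +15.8 points at 90%. For +13.7 and +18.1 points it gives 60.3 and 59.9. Two groups at the larger figures need about 160 children, and two at the smaller figures about 120. With 80 in total, at most one group could have the 60-participant figures (a split of about 60 to 20), and then the other would not.

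**Step 3: power per age group.** The split is an assumption, so a range is shown.

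| Children in the age group | +12.0 points, ψ = 15% | +15.8 points, ψ = 20% |
|---|---|---|
| 24 | 32% | 40% |
| 30 | 39% | 49% |
| 40 | 50% | 62% |
| 50 | 60% | 72% |
| 56 | 65% | 77% |

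At 40 per group the first case is (0.12 × 6.325 − 0.759) / 0.368 ≈ 0, and Φ(0) = 50%. Enumerating the test itself at n = 40 gives 31% (exact) and 46% (mid-p) for +12.0 points, and 51% (exact) and 63% (mid-p) for +15.8 points.

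**Step 4: what 40 children could detect.** At 20% discordance, 80% power needs 19.2 points by the formula and 19.5 by the exact test. At 15% discordance the largest possible difference is 15 points, when every change is a gain. Power there is 70% by the formula, 57% exact and 74% mid-p.

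**Step 5: what an overall rejection can mean.** Take 40 children per group, one gaining 24 points with 25% discordant, the other gaining nothing with 5% discordant. The averages are (24 + 0)/2 = 12 points and (25 + 5)/2 = 15%, which is the Section 9.2 scenario. The overall test is significant in 86% of trials (uncorrected) or 79% (exact). If 15% are discordant in the group without a gain, the rates are 71% and 62%. These discordance rates are assumptions.

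**The case against.** **The overall question is a stated one.** Section 2.2.1 opens with a general objective, and Section 1.4 likewise gives a single primary objective: whether an enhanced schedule improves the response. Section 9.2 compares the standard number of doses with the extra dose, which fits that objective. This stands. It would be wrong to say that the quoted figures answer no question in the protocol.

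**The protocol nowhere says that the age groups are pooled.** This also stands. Pooling is a natural inference from power on total N and from a single named test, but Section 9.1 frames the comparison by age, and a statistical analysis plan might separate the groups. That would leave the power statement uncorrected, since separating the groups cannot raise the power of either.

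**One age group might have a quoted power.** With about 60 of the 80 children in one group, that group would have the 60-participant figures. So a reader should not infer that neither age-specific question could have any of the quoted power; the documents support only that both cannot.

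**A reader might infer that 80% power is impossible at 40 children and 15% discordance.** That depends on the form of the test. It holds for the formula, exact and mid-p versions, but the uncorrected chi-square McNemar test reaches 87% if every change is a gain. That case is extreme, but Section 9.2 does not name the form.

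**Recruitment is limited by one hospital's caseload.** Section 3.7 says so. This is a reason not to ask for more children; it does not make the stated power apply to each age group.

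**Conclusion.** The point holds as a misstatement of what the power figures cover. The arithmetic in Section 9.2 is right for one overall extra-dose comparison. Objectives (a) and (b) cannot both have that power with 80 children in total, whatever the split. The per-group sizes rest on assumed splits. At 40 and 40, power is 50% rather than 80% for +12.0 points, and 62% rather than 90% for +15.8 points, with the exact test lower in both cases. At 50 and 30, power for +12.0 points is 60% and 39%. As Section 9.3 is worded, a rejection over all children would not show which schedule works. The wording does not establish that such a combined test is the intended primary analysis.

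**What to change.** **Section 9.2.** State that the quoted figures apply only to the overall comparison of the extra dose with the standard number of doses. Add power per age group over a range of plausible splits, computed for the form of the test that will be used. For 40 children, for example: about 19 to 20 points for 80% power at 20% discordance (formula or exact test), and at 15% discordance power of at most 70% by the formula and 57% by the exact test.

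**Section 9.3.** State that the McNemar test, in its exact or mid-p form, is run separately at 9 years and over for objective (a) and under 9 years for objective (b). State that the overall result will not by itself be used to support either schedule.

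**Optional.** A within-child ratio of geometric mean titres (after the extra dose over after the standard doses), with a 95% confidence interval per age group, would use the same sera. Section 9.3 already plans geometric means and fold increases, so this is a refinement and the point does not depend on it.

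**Cost.** Two paragraphs reworded and a less favourable stated power. No extra patients, visits or samples.

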### **9.3 Statistical analysis**

The primary immunogenicity endpoints will be the percentage of participants achieving seroprotection and seroconversion. To assess if the extra vaccination dose improves immunogenicity, a McNemar test will be used to assess the

difference in these percentages as calculated from the immunogenicity status obtained after the last two doses of each individual. We will also evaluate geometric mean titers of HI antibodies at baseline and after vaccination. The geometric mean fold increase (GMFI), with 95% confidence intervals, will be calculated for each strain, using a log-normal approximation for the distribution of HI antibody levels pre and post vaccination.

Multivariate logistic regression models will be used to assess the influence of clinically relevant demographic and immunological variables to predict seroconversion to each influenza vaccine strain and complete seroconversion to all strains of the vaccine. Linear regression analyses of log-transformed HI antibody titers and log-transformed T-lymphocyte IFN- $\gamma$  levels will be undertaken to assess the influence of clinically relevant variables on humoral and cellular responses to vaccination, respectively.

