## ABSTRACT

Influenza is a common seasonal infection associated with significant morbidity, mortality and prolonged hospitalisations among children undergoing treatment for cancer. Currently, all children in Australia aged 6 months to 18 years undergoing immunosuppressive therapy, such as treatment for cancer, are recommended to receive annual influenza vaccination.

The current immunisation schedule is supported by scientific evidence demonstrating safety, efficacy and clinical benefit of the inactivated influenza vaccine in immunocompromised children undergoing treatment for cancer. However, immunogenicity is reduced compared to the healthy population. Studies in immunosuppressed adults undergoing treatment for haematological malignancies suggest enhanced response to the influenza vaccine when given repeatedly.

In this study we propose that the inactivated influenza vaccine response in children and adolescents who are being treated for cancer could be improved by introducing an additional vaccine dose to the current one-dose schedule in patients  $\geq 9$  years of age, and the two-dose regimen in patients  $< 9$  years of age. We also propose that developing an additional laboratory method of assessing the cellular immune response to the influenza vaccine could be of benefit, given the limitations of the standardised antibody response in immunosuppressed populations. In addition, the study design will allow assessment of predictors of influenza vaccine immune response with the aim of optimising timing of the vaccination.

The safety of an enhanced influenza vaccine schedule in children undergoing treatment for cancer will be closely monitored by an independent advisory committee composed of several specialists from related paediatric disciplines. Participants in the  $< 9$  years of age group will be informed about the novelty of the approach and need for enhanced monitoring. Participants aged 6 to 35 months will only receive an additional influenza vaccine if an initial safety run in of the enhanced schedule conducted in children 3 to  $< 9$  years of age is determined to be safe and tolerable.

It is estimated that 80 subjects will be recruited over the study period. This is based on the incidence and prevalence of patients diagnosed and receiving treatment for cancer at Perth Children's Hospital Haematology and Oncology Department.

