### **1.3 Standard evaluation of influenza vaccine response**

The rise in influenza-specific hemagglutinin inhibition (HI) antibody titers in pre- and post-vaccination serum is used as a measure of the immune response to the vaccine. Sero-protection in an individual is defined as a post-vaccination HI titer of ≥40. Seroconversion is defined as either a fourfold increase in HI antibody titer if the

pre-vaccination titer was  $\geq 10$  or a rise in HI titer from  $< 10$  to  $\geq 40$  following vaccination.

The Committee for Proprietary Medicinal Products (CPMP) have established criteria to determine whether the influenza vaccine is considered to elicit an effective overall immunogenic response in a population (25). According to these criteria, the influenza vaccine is considered effective if it meets one of the following three criteria: seroprotection in  $> 70\%$  of patients; seroconversion in  $> 40\%$  of patients; or a geometric mean fold increase (GMFI)  $> 2.5$ .

In the study by Kotecha *et al.*, the inactivated trivalent influenza vaccine containing the H3N2, H1N1 and B strains was considered to be immunologically effective by satisfying the criteria for a GMFI increase of  $> 2.5$  for all three vaccine strains. However, the vaccine did not meet efficacy criteria for seroprotection (H3N2 55%, H1N1 61% and B strain 41%) and seroconversion for the B strain (H3N2 43%, H1N1 43%, B strain 33%). In comparison, a recent multicentre open label study of inactivated monovalent H3N2 vaccine in healthy children aged 6 months to 17 years achieved seroprotection in 74% and 88% of children in the 3-8 year and 9-17 year old cohorts; while 72% and 85% seroconverted, respectively. In the same study, children aged 6 to 35 months showed a much lower response in general. Seroprotection and seroconversion were achieved in 19% and 38% of those that received one and two doses of the inactivated H3N2 vaccine, respectively. A group of children aged 6 to 35 months received one or two double doses of the vaccine (an equivalent of one or two standard doses for children  $\geq 3$  years old). These children achieved seroprotection and seroconversion in 30% and 47% of study participants, demonstrating an enhanced response (26). Overall, the data suggests room for improvement with regards to vaccine efficacy and identifying the ideal method with which to measure vaccine response in immunocompromised children with cancer.

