#### **1.4 Enhanced influenza vaccination schedule and extended vaccine response evaluation**

The primary objective of our study is to determine whether an enhanced influenza vaccine schedule could further improve the immune response to the inactivated influenza vaccine in children receiving treatment for cancer.

We hypothesise that introduction of a two-dose inactivated influenza vaccine schedule will enhance the immune response in immunocompromised children and adolescents  $\geq 9$  years of age undergoing therapy for cancer, compared to the current one-dose schedule. This is in keeping with findings of a few studies performed in adolescent and adult patients with secondary immune deficiencies such as HIV or treatment for haematological malignancies, where repeated influenza vaccination resulted in optimised seroprotection (28-30).

We also aim to test whether a three-dose schedule of the inactivated influenza vaccine will provide a superior immune response compared to the currently recommended two-dose influenza vaccine schedule in immunocompromised children  $< 9$  years of age undergoing therapy for cancer. Only one study has previously attempted to assess the benefit of a three-dose schedule in children with cancer, however the outcomes of this study are limited as it was conducted over 35 years ago in a small patient cohort (31).

We will evaluate the safety of the additional dose of influenza vaccine by closely monitoring and reporting adverse events (AEs), and appointing an independent Data Safety Monitoring Board (DSMB) to ensure study participant safety. For safety reasons, children aged 6 to 35 months will not receive the additional influenza vaccine until an initial safety run in phase determines safety and tolerability of the third dose in children aged 3 to  $< 9$  years of age.

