#### **8.3.4 Data Safety Monitoring Board (DSMB)**

To ensure the safety of all study participants, a Data Safety Monitoring Board will be appointed. The DSMB will consist of five specialists from the following paediatric disciplines: Oncology, Haematology, Infectious diseases, Immunology and Neurology; as well as a Statistician.

The DSMB will receive a report issued by the study investigators every two weeks or at the completed recruitment of every 10 newly vaccinated study participants, regardless of the degree of possible AEs. In addition, the DSMB will receive a safety report after 6 participants have received the third dose of the vaccine in the 3 – <9 year age group and based on the safety outcomes of this report will provide a recommendation as to whether recruitment to the three dose schedule can commence in the 6-35 month age group.

Any unexpected, severe or serious AEFIs will be reported to the DSMB by the study investigators within the set timelines. The DSMB may recommend the study to be modified or terminated based on the reported events.

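### Section 9.3 pairs each participant's last two doses, so a child under 9 who stops at two doses would be tested as dose 2 against dose 1, contrary to Sections 9.1 and 9.2

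*Protocol*

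**What the plan says.** Section 9.3 gives the purpose of the primary test, "To assess if the extra vaccination dose improves immunogenicity, a McNemar test will be used to assess the", and completes the sentence with the pairing rule: the "difference in these percentages as calculated from the immunogenicity status obtained after the last two doses of each individual". Nothing there requires the last dose to be the extra dose.

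Section 9.1 gives the primary contrast for the younger group as "years of age comparing three doses to two doses". Section 9.2 bases the sample size on paired status "after the standard number of doses and the extra dose, respectively".

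The protocol also foresees children under 9 who stop at two doses. The Abstract says "Participants aged 6 to 35 months will only receive an additional influenza vaccine if an initial safety run in of the enhanced schedule conducted" in older children is found safe. Section 1.4 says "children aged 6 to 35 months will not receive the additional influenza vaccine until an initial safety run in phase determines safety and tolerability" of that dose in the 3 to under 9 group. Section 8.3.4 ties the recommendation to a "safety report after 6 participants have received the third dose of the vaccine" in that group. Section 8.4 can end additional doses altogether. Sections 3.6 and 5.2 recheck eligibility, fitness and neutrophil count around each vaccination.

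**The concern.** The test is meant to isolate the extra dose. For a child under 9 with only two doses, the last two doses are the current standard schedule, so the pair measures the step from dose 1 to dose 2. Section 1.2 reports that two doses already do significantly better than one in children under 9 with cancer. Pairs of this kind therefore push the result one way, towards the extra dose, and could help produce a positive finding even if the third dose adds nothing.

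The rule also treats the age groups differently. A participant aged 9 or over who misses the extra dose has only one post-dose status and drops out of the paired test. A child under 9 who misses it stays in, with a different contrast.

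**Working it through.** **Can such a pair exist?** HI samples are drawn at Visit 2 (after dose 1, before dose 2) and, in children under 9, at Visit 3 (after dose 2, before dose 3), per Sections 5.3.2 and 5.3.3. The footnote in 5.3.3 makes the third dose conditional at 6 to 35 months, not the Visit 3 sample. A two-dose child can therefore have a complete dose 1/dose 2 pair. No section excludes it.

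**The plan's own figures.** For the McNemar test, n = [z(1−α/2)·√p + z(power)·√(p − d²)]² / d², with p the discordant proportion and d the gain. With two-sided α = 0.05 (Section 9.2 does not state sidedness):
- p = 0.15, d = 0.137, 80% power: n = 60.3 (stated 60)
- p = 0.15, d = 0.120, 80% power: n = 79.4 (stated 80)
- p = 0.20, d = 0.181, 90% power: n = 59.9 (stated 60)
- p = 0.20, d = 0.158, 90% power: n = 79.9 (stated 80)

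The sample size figures reproduce and are not in dispute.

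**Inputs for the bias.**
- N = 80 pairs, pooled over age groups as in Section 9.2.
- True extra-dose effect: zero (assumption, to measure false success).
- Participants with the extra dose: 15% discordance, as in Section 9.2, split evenly (7.5% up, 7.5% down).
- Two-dose-only children under 9: number m is not in the protocol, so it is varied.
- Second-dose gain: Section 1.3 says "Seroprotection and seroconversion were achieved in 19% and 38% of those that received one and two doses", so 38 − 19 = 19 points. These were healthy children aged 6 to 35 months given a monovalent H3N2 vaccine. The protocol gives no dose 1/dose 2 rates for children with cancer, so 10 points is added as a lower assumption. With an assumed 2.5% loss, the up/down probabilities are 21.5%/2.5% and 12.5%/2.5%.

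**Spurious gain** = (m/80) × second-dose gain. **False success** = share of simulated trials in which the two-sided 5% McNemar test rejects in favour of the extra dose.

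| m of 80 | Second-dose gain | Spurious gain | False success, uncorrected test | False success, exact test |
|---|---|---|---|---|
| 0 | – | 0 | 2.2% | 1.2% |
| 4 | 19 points | 4/80 × 19 = 0.95 points | 3.5% | 2.0% |
| 8 | 19 points | 8/80 × 19 = 1.9 points | 5.4% | 3.3% |
| 16 | 19 points | 16/80 × 19 = 3.8 points | 11.5% | 7.6% |
| 24 | 19 points | 24/80 × 19 = 5.7 points | 21% | 15% |
| 8 | 10 points | 8/80 × 10 = 1.0 point | 3.6% | 2.1% |
| 16 | 10 points | 16/80 × 10 = 2.0 points | 5.8% | 3.5% |

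The nominal rate in this direction is 2.5%.

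**The case against.** The best defence is that the rest of Section 9 makes the intent plain. Sections 9.1 and 9.2 both describe extra dose against standard schedule, and the 9.3 sentence itself opens with the extra dose. On that reading the phrase is shorthand covering 2 against 1 and 3 against 2 at once. This stands as to intent. A reader might infer that the sponsor plans to pool two-dose-only children into the primary test; the documents do not support that. What remains is that 9.3 fixes the operational rule in words that contradict the aim, and an analysis plan following it literally would inherit the fault. This is a wrong definition, not a detail left for later.

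The number affected may also be small. The run-in needs six children, and the study period in Section 3.8 with vaccine available from March or April (Section 6.1) may span two seasons, so young children vaccinated after a favourable decision would be unaffected. Section 8.3.4 speaks of starting recruitment of the youngest group to the three-dose schedule only after that decision, which could be read as keeping them out beforehand. The Abstract, the design schema and Section 5.3.3, however, make the dose conditional, not enrolment. This limits the likely size but does not remove the problem.

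Finally, the 19-point gain is borrowed from healthy children and one vaccine, and may not carry over. That is accepted; hence the 10-point rows.

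**Conclusion.** The pairing rule in Section 9.3 conflicts with Sections 9.1 and 9.2 and, taken literally, credits the second-dose gain to the extra dose. Under the assumptions above, false success stays near nominal if about 4 of 80 participants are affected, roughly doubles relative to nominal at 8 (5.4%), and reaches 11.5% at 16 and 21% at 24. At a 10-point gain it is 3.6% at 8 and 5.8% at 16. The bias is minor if few children stop at two doses and serious if dose 3 is withheld from an age group.

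A reader might conclude that the primary result is bound to be seriously biased. The documents do not support that: they do not say how many children will stop at two doses, and they give no second-dose gain for children with cancer. The direction of the bias is firm; its size is not. Severity: should be fixed.

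**What to change.** Replace the last-two-doses phrase in Section 9.3 with fixed time points that match 9.1 and 9.2:
- 9 years and over: Visit 2 (after dose 1) against Visit 3 (after dose 2).
- Under 9 years: Visit 3 (after dose 2) against Visit 4 (after dose 3).

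Include participants who received the extra dose and have both samples. Report children under 9 with two doses only separately and descriptively.

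The cost is one sentence and some pairs. At 15% discordance and 80% power, the detectable gain rises from 12.0 points with 80 pairs to about 12.6 if 8 leave (72 pairs) or 13.3 if 16 leave (64 pairs). Power for a 12.0-point gain falls from 80% to 76% or 71%. The pairs lost carry no information on the extra dose.
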